# Multicentre, prospective, randomised, open-label, blinded end point trial of the efficacy of allopurinol therapy in improving cardiovascular outcomes in patients with ischaemic heart disease: protocol of the ALL-HEART study

**DOI:** 10.1136/bmjopen-2016-013774

**Published:** 2016-09-08

**Keywords:** allopurinol, cardiovascular outcomes, quality of life, uric acid

## Abstract

**Introduction:**

Ischaemic heart disease (IHD) is one of the most common causes of death in the UK and treatment of patients with IHD costs the National Health System (NHS) billions of pounds each year. Allopurinol is a xanthine oxidase inhibitor used to prevent gout that also has several positive effects on the cardiovascular system. The ALL-HEART study aims to determine whether allopurinol improves cardiovascular outcomes in patients with IHD.

**Methods and analysis:**

The ALL-HEART study is a multicentre, controlled, prospective, randomised, open-label blinded end point (PROBE) trial of allopurinol (up to 600 mg daily) versus no treatment in a 1:1 ratio, added to usual care, in 5215 patients aged 60 years and over with IHD. Patients are followed up by electronic record linkage and annual questionnaires for an average of 4 years. The primary outcome is the composite of non-fatal myocardial infarction, non-fatal stroke or cardiovascular death. Secondary outcomes include all-cause mortality, quality of life and cost-effectiveness of allopurinol. The study will end when 631 adjudicated primary outcomes have occurred. The study is powered at 80% to detect a 20% reduction in the primary end point for the intervention. Patient recruitment to the ALL-HEART study started in February 2014.

**Ethics and dissemination:**

The study received ethical approval from the East of Scotland Research Ethics Service (EoSRES) REC 2 (13/ES/0104). The study is event-driven and results are expected after 2019. Results will be reported in peer-reviewed journals and at scientific meetings. Results will also be disseminated to guideline committees, NHS organisations and patient groups.

**Trial registration number:**

32017426, pre-results.

Strengths and limitations of this studyThe ALL-HEART study is a large prospective randomised study designed to answer the question of whether allopurinol improves cardiovascular outcomes in patients with ischaemic heart disease.The trial is conducted within the normal UK healthcare setting, providing good external validity. The end point committee is blinded to treatment allocation.One limitation of the study is that it does not include patients with ischaemic heart disease who are younger than 60 years old.

## Introduction

The ALL-HEART study is an academic clinical trial that aims to address whether allopurinol added to usual therapy improves cardiovascular (CV) outcomes in patients with ischaemic heart disease (IHD).

IHD is one of the most common causes of death in men and women in the UK and most other developed countries.^1^ Although death rates from IHD have fallen in the past 10 years, largely due to reductions in smoking and improvements in treatment and secondary prevention, morbidity from IHD is increasing. Patients with IHD often have reduced quality of life due to symptoms, limitation of activities and psychological impact of the disease. IHD is usually treated with a combination of medications, some of which improve symptoms and some of which improve survival. In addition, interventional procedures such as angioplasty, coronary artery stenting and coronary artery bypass grafting are used in selected patients.

Allopurinol is a xanthine oxidase inhibitor that lowers uric acid levels and is licensed for the prevention of gout, but is not currently indicated for treating asymptomatic hyperuricaemia. Allopurinol is usually given in doses of 100–900 mg daily. Xanthine oxidase promotes oxidative stress which inactivates the antiatherosclerotic substance nitric oxide. Xanthine oxidase levels are raised in several conditions including coronary artery disease.^2^ Allopurinol has several beneficial effects in CV disease. It improves endothelial function in patients with heart failure,^3^
^4^ type 2 diabetes^5^ and smokers,^6^ reduces left ventricular mass in patients with IHD^7^ and reduces left ventricular hypertrophy in patients with type 2 diabetes mellitus^8^ and chronic kidney disease.^9^ It also lowers blood pressure and decreases arterial stiffness and carotid intima-media thickness progression.^7^
^10–13^ Allopurinol reduces the troponin rise in patients undergoing percutaneous coronary intervention following ST elevation myocardial infarction (MI), which is strong evidence that downstream ischaemic cardiomyocytes stay alive better during an ischaemic insult in the presence of allopurinol therapy.^14^ In patients with angina and angiographically documented coronary artery disease, allopurinol 600 mg daily has anti-ischaemic activity in that it increases exercise time and reduces chest pain.^15^

In earlier observational studies in patients with hyperuricaemia^16^ and heart failure,^17^
^18^ allopurinol use was associated with reduced mortality. In recent case–control studies, allopurinol use was associated with a reduced risk of MI^19^ and a reduced risk of non-fatal MI.^20^ In a recent cohort study in patients with hyperuricaemia, patients on allopurinol treatment had a lower risk of MI, stroke or CV death and a lower risk of all-cause mortality compared with non-users of allopurinol.^21^ A study conducted in the UK Clinical Practice Research Datalink in patients aged over 65 years with hypertension showed that allopurinol use was associated with a significantly lower risk of stroke and cardiac events than in non-exposed control patients. In this study, treatment with higher dose allopurinol (defined as 300 mg daily) was associated with a significantly lower risk of stroke and cardiac events than treatment with a lower dose of allopurinol.^22^ In patients with hypertension and impaired renal function, allopurinol use was associated with a lower risk of developing CV disease and all-cause mortality.^23^ A long-term follow-up study of a 2-year randomised trial of 113 patients with chronic kidney disease showed that long-term treatment with allopurinol may slow the rate of progression of kidney disease and reduce CV risk.^24^
^25^

Various mechanisms have been suggested as to how allopurinol may improve CV outcomes. Xanthine oxidase is a major source of reactive oxygen species.^26^ Allopurinol profoundly reduces oxidative stress by reducing superoxide anions and other free radicals, which reduces cardiac hypertrophy, increases tissue oxygenation and reduces atherosclerotic plaque rupture which is involved in MI.^27–30^ Allopurinol may also reduce cardiac afterload by improving arterial compliance through reduced wave reflection and improved endothelial function. It is not clear whether it is uric acid lowering or other effects of allopurinol that are important, although in one study comparing allopurinol with the uricosuric agent probenecid, effects on endothelial function were only seen with xanthine oxidase inhibition and not by reducing uric acid with probenecid.^27^ Finally, by inhibiting xanthine oxidase activity, allopurinol increases levels of hypoxanthine, which might increase ATP levels and thus energy availability to tissues. Extra ATP and oxygen availability produced by allopurinol might prevent downstream ischaemic cardiomyocytes from infarcting and thereby leading to heart failure during an ischaemic insult such as acute coronary syndrome (ACS).^31^
^32^

Some studies have suggested that higher doses of allopurinol (often 600 mg daily) are necessary to achieve some of the positive CV effects,^6–8^
^15^
^22^
^27^ which is why a dose of 600 mg daily was selected for participants with normal renal function at baseline for the current study. It has previously been demonstrated that this can be given safely in patients with angina.^15^

Most of the papers in this field still conclude that there is a need for large randomised controlled trials to answer the question of whether allopurinol is beneficial in patients with CV disease. The ALL-HEART study is the key outcome study that will provide the answer to this question in patients with IHD, in addition to providing robust data on any improvements in quality of life and an analysis of the health economics of the use of allopurinol in the UK National Health Service (NHS) in patients with IHD.

## Methods and analysis

### Objectives

The primary objective of the study is to determine whether the addition of allopurinol (up to 600 mg daily) to usual therapy improves CV outcomes. The secondary objectives are to determine the cost-effectiveness of adding allopurinol to usual therapy, to determine whether allopurinol improves quality of life and to determine the safety and tolerability of giving allopurinol to patients with IHD (without a history of gout).

### Outcomes

The primary outcome is the composite CV end point of non-fatal MI, non-fatal stroke or CV death. The secondary outcomes are non-fatal MI; non-fatal stroke; CV death; all-cause mortality; all CV hospitalisations; hospitalisation for ACS (includes hospitalisation for MI and for troponin-negative cardiac chest pain); coronary revascularisation; hospitalisation for ACS or coronary revascularisation, hospitalisation for heart failure, quality of life (EQ-5D and Seattle Angina Questionnaire); cost-effectiveness of allopurinol. Data will also be collected on the safety and tolerability of allopurinol in patients with IHD, in particular, discontinuations of allopurinol due to adverse events including gout flares and serious adverse skin reactions.

### Ethics and trial registration

The study received approval from the UK Medicines and Healthcare products Regulatory Agency (MHRA), local research and development departments and the national Caldicott guardian in Scotland. Patient recruitment to the study started on 7 February 2014. The trial was prospectively registered in ISRCTN (ISRCTN32017426; 16 August 2013) and EudraCT (2013-003559-39; 19 September 2013). Protocol amendments will be approved by the ethics committee and regulatory authorities as per current guidelines and will be communicated to investigators and the primary trial registry by the study team.

### Study design

The study is a multicentre, controlled, prospective, randomised, open-label, blinded end point (PROBE) superiority trial of allopurinol (up to 600 mg daily) versus no treatment added to usual therapy in patients aged 60 years and over with IHD. The study is end point driven and will end when the required number of adjudicated primary end points have occurred.

#### Number of participants

In total, 5215 patients will be randomised in a 1:1 ratio to allopurinol or no additional treatment (figure 1). Patients will be recruited from the UK. Approximately 290 primary care practices will be involved, and the study will be coordinated by two main study sites (Dundee, Scotland and Nottingham, England). Recruitment was initially expected to last for ∼2 years with an expected average follow-up period of 4 years. The recruitment phase was extended in 2016 and the follow-up phase may be extended depending on recruitment rates and event rates.

**Figure 1 BMJOPEN2016013774F1:**
[figure not shown]
ALL-HEART study overview. In total, 5215 patients aged over 60 years with ischaemic heart disease will be randomised to receive allopurinol or no additional therapy, in addition to their usual care, then followed up for an expected average of 4 years for outcomes.

#### Identification of participants, screening visit and randomisation

Primary care practice lists are searched for suitable patients with IHD who are invited to participate. Other patients with IHD who volunteer to take part in the trial may be included. Patients may also be invited to participate from secondary care clinics and consented research databases. At a screening visit, written informed consent is taken by a research nurse (or doctor), inclusion and exclusion criteria checked (box 1) and blood samples taken for baseline full blood count, urea and electrolytes, creatinine, estimated glomerular filtration rate (eGFR) and urate. Baseline demographics, medical history, CV risk factors, medication, blood pressure and height and weight data are collected.
Box 1Inclusion and exclusion criteria*Inclusion criteria:*
Male or female patients aged 60 years and over.Ischaemic heart disease (IHD) defined as a diagnosis of angina or myocardial infarction at any time or other evidence of IHD (investigator opinion).*Exclusion criteria:*
History of gout.*Known severe renal impairment (estimated glomerular filtration rate (eGFR) <30 mL/min).Moderate-to-severe heart failure (New York Heart Association III–IV).Significant hepatic disease (eg, alanine transaminase>3× upper limit of normal, cirrhosis, ascites; investigator opinion).Patients currently taking part in another interventional clinical trial of an investigational medicinal product or medical device (or taken part in one within the past 3 months).Previous allergy to allopurinol.Previous serious adverse cutaneous (skin) reaction to any drug (eg, Stevens Johnson syndrome, toxic epidermal necrolysis, hospitalisation due to skin reaction to drug; investigator opinion).Patients already taking urate-lowering therapy (including allopurinol, febuxostat, sulfinpyrazone, benzbromarone, probenecid, rasburicase).Patients taking azathioprine, mercaptopurine, ciclosporin or theophylline.Malignancy (except non-metastatic, non-melanoma skin cancers, cervical in situ carcinoma, breast ductal carcinoma in situ, or stage 1 prostate carcinoma) within the past 5 years (investigator opinion).*Exclusion criterion 2 was previously ‘known renal impairment eGFR<60 mL/min’ for patients recruited from the start of the trial (7 February 2014) until 4 April 2016 when protocol v4 was implemented at all study sites. Fifty-two per cent of the target number of patients had been randomised by this date.

Two different quality of life questionnaires are completed at the screening visit—the EQ-5D^33^ to assess general health outcomes and the Seattle Angina Questionnaire^34^ to assess coronary artery disease-specific quality of life. The EQ-5D is a standardised instrument for use as a measure of health outcome. Applicable to a wide range of health conditions and treatments, it provides a simple descriptive profile and a single index value for health status. The Seattle Angina Questionnaire is a disease-specific self-administered functional status measure for patients with coronary artery disease. It measures five clinically important dimensions of health in patients with coronary artery disease (anginal stability, anginal frequency, physical limitation, treatment satisfaction, quality of life) and is sensitive to clinical change over time. The (UK) English version is used.

Data are recorded on a secure dedicated electronic case report form (eCRF) and study web portal with a central database at the Robertson Centre for Biostatistics, University of Glasgow. Patients are randomised via a web portal based at the Robertson Centre for Biostatistics, University of Glasgow or interactive voice response system in a 1:1 ratio to either allopurinol or no drug to be given in addition to their usual medications. No placebo is used in the study; the comparator arm is usual care. Randomisation is stratified by primary care practice, history of MI and history of stroke, with treatment group allocated according to randomly permuted blocks of variable size. The allopurinol (oral tablet) is prescribed generically by the primary care physician.

In patients with screening visit blood results showing eGFR≥60 mL/min, allopurinol is started at 100 mg daily for 2 weeks, then titrated to 300 mg daily for 2 weeks, then 600 mg daily (given as 300 mg twice daily) if tolerated. Allopurinol is then continued at 600mg daily, given as 300mg twice daily, (or the maximum tolerated dose if lower) throughout the duration of the study for up to 5 years. In patients with screening visit blood results showing eGFR 30–59 mL/min, allopurinol is started at 100 mg daily for 2 weeks, then titrated to 300 mg daily if tolerated. Allopurinol is then continued at 300 mg daily (or the maximum tolerated dose if lower) throughout the duration of the study for up to 5 years.

Patients with screening visit blood results showing eGFR 30–59 mL/min were only included in the study from 4 April 2016 onwards following implementation of a protocol amendment that aimed to improve recruitment, enrich the study population and increase the generalisability of the results. Owing to a temporary UK shortage of allopurinol 100 mg tablet supply experienced in 2014, the protocol was amended to allow patients to start on 100–150 mg allopurinol for the first 2 weeks. The dose was then uptitrated as above. The usual starting dose of allopurinol for the majority of patients in the study was 100 mg.

Blood tests are sent to local NHS laboratories and results are checked and entered into the eCRF by study nurses. General practitioners (GPs) are alerted to any abnormal blood results. All patients are asked to report any adverse events, particularly rash or gout flares. GPs are also asked to report any serious adverse events that come to their attention during the trial. Patients experiencing a rash that could be due to allopurinol are withdrawn from allopurinol therapy. Patients withdrawing from allopurinol therapy are encouraged to still complete the planned follow-up within the study. Reasons for withdrawal from randomised therapy are recorded. Temporary withdrawals of allopurinol therapy are allowed at the discretion of a physician and reasons are documented. Dose changes are also allowed at the discretion of a physician at any time during the study (up to the maximum doses specified within the protocol). Any dose changes are recorded on the study eCRF and reasons documented. Patients undergo usual concomitant care during their participation in the trial and no interventions are prohibited during the trial.

Adverse reactions in association with allopurinol are rare in the overall treated population and mostly of a minor nature. The incidence of adverse reactions is thought to be higher in the presence of renal and/or hepatic disorders. The most common adverse reaction to allopurinol is rash (affects around 1% of patients). Usually this is a minor rash that resolves on stopping therapy. Rarely, the rash may be more serious and occasionally serious skin reactions such as Stevens Johnson syndrome or toxic epidermal necrolysis may occur. In the event of a serious skin reaction, allopurinol therapy should be stopped immediately and should not be restarted. Other possible adverse reactions to allopurinol include gastrointestinal disturbance such as nausea or vomiting, asymptomatic increases in liver function tests, hypersensitivity, angio-oedema and hepatitis. The summary of product characteristics lists other possible adverse reactions to allopurinol.

All serious adverse events are collected (whether thought to be related to randomised therapy or not). Non-serious adverse events (non-serious adverse reactions) are only collected if thought to be possibly, probably or definitely related to randomised therapy. Data on occurrence of skin rashes and gout flares are collected from all patients in the study. If any patients randomised to the non-allopurinol arm of the study later start allopurinol therapy for clinical reasons, this is recorded on the eCRF along with the reasons. At the end of the trial, patients will stop allopurinol therapy and will continue to receive usual care.

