## Data analysis and statistical methods

### Sample size

In total, 5215 patients will be randomised to give 80% power to detect a 20% reduction in the primary CV end point for the intervention (allowing for 4% dropout for withdrawal of consent to follow-up and for non-CV deaths). A 14% event rate over 4 years average follow-up has been estimated from previous trials in similar patient groups. The study will end when 631 adjudicated primary end points have occurred.

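### The 5-year limit on allopurinol matches the initial timetable, but not the extended, event-driven trial, which is projected to follow its earliest patients for about 5.7 to 6.0 years

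*Protocol article*

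**What the plan says.** Under Identification of participants, screening visit and randomisation, the protocol article sets the maintenance dose for patients with eGFR of 60 mL/min or more, and again for those with eGFR 30–59 mL/min. Both times treatment continues "throughout the duration of the study for up to 5 years". The same section later ties stopping to the close of the study: "At the end of the trial, patients will stop allopurinol therapy and will continue to receive usual care".

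That close is a number of events, not a date. Study design states: "The study is end point driven and will end when the required number of adjudicated primary end points have occurred". Sample size gives the number: "The study will end when 631 adjudicated primary end points have occurred".

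Number of participants first expected about 2 years of recruitment "with an expected average follow-up period of 4 years", and then adds: "The recruitment phase was extended in 2016 and the follow-up phase may be extended depending on recruitment rates and event rates". The footnote to Box 1 dates the change of the renal exclusion criterion to 4 April 2016 and says: "Fifty-two per cent of the target number of patients had been randomised by this date".

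**The concern.** Continuing throughout the study and continuing for at most 5 years are the same instruction only if nobody is followed for longer than 5 years. That held under the initial timetable. It is not expected to hold once recruitment is longer and the end is set by events.

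Two readings are then open. The 5 years may be an outdated statement of study length, or it may be a cap for each patient. They lead to different treatment after year 5, and the article does not say which is meant. The drug is prescribed by primary care physicians, so a literal reading could be acted on.

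Under the cap reading, the earliest allopurinol patients would come off the drug before the trial ends. The article wants follow-up to go on after the drug is stopped ("Patients withdrawing from allopurinol therapy are encouraged to still complete the planned follow-up within the study"), and the primary analysis is intention-to-treat. Events after year 5 would therefore count in the allopurinol arm without treatment. That is planned, avoidable dilution in one arm only.

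**Working it through.** **Inputs from the article**
- N = 5215, 1:1; 631 events; 80% power for a 20% reduction (HR 0.80); 14% event rate over 4 years; 4% dropout (Sample size; Number of participants).
- Recruitment started on 7 February 2014 (Ethics and trial registration); 52% randomised by 4 April 2016 (Box 1 footnote). The interval is 787 days, or 2.15 years.

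**Assumptions**
- Two-sided 5% significance level (not stated; it fits the 95% CIs).
- Exponential event times, and uniform entry within each recruitment phase.
- The remaining 48% enter over 1 to 2 further years. The article gives no new end date. Two years is about the pace up to April 2016, since 2.15/0.52 = 4.14 years in total.

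**1. The plan's own figures**

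Schoenfeld: events = 4(1.960 + 0.842)² / (ln 0.80)² = 631, as stated.

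N = 631 / [(0.14 + 0.112)/2] / 0.96 = 5217, against 5215. So 14% is the control-arm risk. Read as the overall risk it would give 631/0.14/0.96 = 4695.

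**2. Longest follow-up from the timetable alone**

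Longest follow-up = mean entry time + average follow-up.
- Initial plan: 2/2 + 4 = 5.0 years.
- Extended, 1 more year: mean entry = 0.52 × 2.15/2 + 0.48 × (2.15 + 0.5) = 1.83, so 5.83 years.
- Extended, 2 more years: mean entry = 0.52 × 2.15/2 + 0.48 × (2.15 + 1.0) = 2.07, so 6.07 years.

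**3. Time of the 631st event**

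Control hazard = −ln(0.86)/4 = 0.0377 per year; allopurinol hazard = 0.80 × 0.0377; loss hazard = −ln(0.96)/4 = 0.0102 per year. For hazard h, loss l and follow-up f, the event probability is h/(h + l) × [1 − exp(−(h + l)f)]. This is averaged over entry times and solved for 631 events.

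| Recruitment | 631st event (years from first randomisation) | Patients with potential follow-up over 5 years |
|---|---|---|
| Initial 2 years | 4.89 | 0% |
| Remaining 48% all enter in April 2016 (lower bound) | 5.49 | 12% |
| 1 more year | 5.74 | 18% (about 463 in the allopurinol arm) |
| 1.5 more years | 5.86 | 21% |
| 2 more years | 5.99 | 24% (about 622 in the allopurinol arm) |

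The percentages go by randomisation date. For 1 more year: 0.52 × (5.74 − 5)/2.15 = 18%. Treating dropout differently (removed at the start, or ignored) widens 5.74–5.99 to about 5.65–6.07.

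**4. Worst case if the limit is applied as a cap**

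The allopurinol hazard returns to the control hazard at 5 years. Between 10 and 18 of the 631 events then fall after year 5 (1.6% to 2.9%), and 1.5% to 2.6% of allopurinol person-time is off treatment. Weighting the log HR by the share of events before year 5:
- 1 more year: (1 − 0.0162) × ln 0.80 = −0.2195, HR 0.803; power = Φ(√(631/4) × 0.2195 − 1.960) = Φ(0.797) = 78.7%.
- 2 more years: (1 − 0.0291) × ln 0.80 = −0.2167, HR 0.805; power = Φ(0.762) = 77.7%.
- No cap: Φ(12.56 × 0.2231 − 1.960) = 80.0%.

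**5. Sensitivity to the control risk (assumed range, 1 to 2 more years)**
- 12%: 35% to 41% of patients pass 5 years; worst-case power about 74% to 76%.
- 16%: 5% to 11% pass; worst-case power about 79.5% to 79.9%.
- Nobody passes 5 years once the control risk exceeds about 17% (1 more year) to 18.3% (2 more years).

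**The case against.** The strongest reply is that the main instruction is to treat for the duration of the study, that the article separately says the drug stops when the trial ends, and that the end is set by events. Read together, these point to treatment until the 631st event, with the 5 years as leftover wording. No sentence describes a patient reaching a limit and continuing untreated; the sentence on continued follow-up concerns patients who withdraw from the drug. On this reading nothing happens to treatment or analysis. That reading is plausible. It does not remove the stated limit, which still contradicts the projected timetable and needs correcting.

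Other points stand in part. The recruitment tail is assumed, so 5.7 to 6.0 years is a projection and not a figure from the trial. At 14% risk, however, the maximum exceeds 5 years even if all remaining patients had entered at once. The first patient does not reach 5 years until February 2019, so an amendment could come in time; the article, which already allows for longer follow-up, says nothing about the treatment limit. The power loss is an upper bound. At these hazards only about 82% of early allopurinol patients would be event-free and in follow-up at year 5 (about 378 of 463, or 508 of 622), and some would already have stopped the drug.

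**Conclusion.** The concern holds, as a minor one. The 5-year limit fits the initial timetable (at most 5.0 years) and not the current design, in which the 631st event is projected at 5.74 to 5.99 years. That rests on the plan's 14% control risk and on 1 to 2 further years of recruitment, which is assumed. Whether the limit is a cap or outdated wording cannot be settled from the article. If it is outdated, the cost is confusion only. If it is a cap, the worst-case loss is about 1 to 2 points of power at the planned event rate, more if events are slower, and none if the control risk is clearly higher than planned.

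**What to change.** Delete the 5-year limit in both dosing sentences and state that allopurinol continues, at the target or maximum tolerated dose, until the event-driven end of the trial. This agrees with the existing sentence on stopping. It is one wording change in two places and needs no extra patients, visits or analyses.

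If a fixed limit is deliberately kept, say that it applies to each patient, restate the power allowing for the expected off-treatment time, and add a sensitivity analysis of the primary outcome that censors both arms at that limit.

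### Non-serious events other than rash and gout flares are kept only if thought related to randomised therapy, so for the named symptoms the usual-care count will be close to empty and the arms cannot be compared

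*Protocol article*

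**What the plan says.** All five places below are in the protocol article.

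- **Collection rule** (Identification of participants, screening visit and randomisation): non-serious adverse events, glossed in parenthesis as reactions, "are only collected if thought to be possibly, probably or definitely related to randomised therapy". The same paragraph makes two exceptions. Serious adverse events are recorded whatever their presumed cause, and "Data on occurrence of skin rashes and gout flares are collected from all patients in the study".
- **Control condition** (same section): patients are randomised "in a 1:1 ratio to either allopurinol or no drug to be given in addition to their usual medications", and "No placebo is used in the study; the comparator arm is usual care".
- **Expected reactions** (same section): rash is named as the most common, at around 1% of patients. The text continues: "Other possible adverse reactions to allopurinol include gastrointestinal disturbance such as nausea or vomiting". It then adds raised liver tests, hypersensitivity, angio-oedema and hepatitis.
- **Objective** (Objectives): safety and tolerability of allopurinol in this population is a secondary objective. Outcomes singles out stopping allopurinol because of adverse events.
- **Contact with patients**: everyone is asked to report adverse events, and the annual questionnaire covers them with no restriction by arm. Only the allopurinol arm has the six-week nurse visit, at which adverse events are recorded.

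**The concern.** Whether a non-serious event is kept depends on a causality judgement, and that judgement depends on the arm. If a patient on allopurinol reports nausea, the drug is an obvious candidate and the event can be called at least possibly related. If a usual-care patient reports the same nausea, no study drug exists to which it could be related, and it drops out. Blinding is described only for end point adjudication, so nothing indicates that relatedness is judged without knowledge of the arm.

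At stake is what can be said about minor symptomatic reactions in a trial with tolerability among its secondary objectives. In patients aged 60 and over, background complaints will be mixed with any drug effect. Without a control count the two cannot be separated. An analysis plan cannot repair this, because the control events would not have been kept.

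**Working it through.** The article gives no expected count for non-serious events, so there is no stated figure to reproduce. The check is a reading of the rules by event type, followed by an illustration of size.

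**1. What is kept in each arm**

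| Event type | Allopurinol | Usual care | Comparable? |
|---|---|---|---|
| Serious adverse events | all | all | yes |
| Skin rash, gout flares | all | all | yes |
| Quality of life (1 year and end of trial) | all | all | yes |
| Other non-serious events | if thought related | if thought related, but no drug allocated | no |
| Stopping allopurinol | recorded | not applicable | one arm only |

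The gap is therefore confined to other non-serious events. Hypersensitivity, angio-oedema and hepatitis are captured in both arms when serious, so in practice the gap is mainly minor gastrointestinal complaints.

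**2. Is the control cell truly empty?** Not strictly. A control patient who later starts allopurinol for clinical reasons could have an event called related. That the count is close to empty is an inference from the rule, not a figure in the article.

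**3. Do the questionnaire and the request to report events undo the filter?** They show that the information is asked for in both arms. The collection rule then says which non-serious events are kept. As written, the rule decides.

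**4. Size, as an illustration only.** Patients per arm: 5215 / 2 = 2607.5. Let r be the true proportion with the symptom over some period, equal in both arms (no drug effect). Let a and b be the proportions of those events judged related in the allopurinol and control arms.

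Recorded count = 2607.5 × r × a on allopurinol and 2607.5 × r × b in control. Spurious risk difference = r × (a − b).

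None of r, a or b comes from the documents.

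| r | a | b | Allopurinol | Control | Difference (points) |
|---|---|---|---|---|---|
| 5% | 20% | 0% | 26 | 0 | 1.0 |
| 5% | 30% | 5% | 39 | 7 | 1.25 |
| 10% | 50% | 0% | 130 | 0 | 5.0 |
| 10% | 50% | 5% | 130 | 13 | 4.5 |
| 20% | 50% | 0% | 261 | 0 | 10.0 |
| 20% | 50% | 5% | 261 | 26 | 9.0 |

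For scale, the article's figure of around 1% for rash corresponds to 0.01 × 2607.5 = 26 patients. The direction holds whenever a exceeds b. The size shrinks in proportion to r and to a − b.

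**The case against.** The strongest reply is that the article never sets out to compare these events. Its parenthesis treats them as adverse reactions, that is, events already attributed to the drug. Primary and sensitivity analyses plans a tabulation of serious events and a description of time to stopping allopurinol, with nothing on non-serious events between arms. Tolerability is approached mainly through discontinuation, and limited collection of minor events is a common, openly stated economy in a large pragmatic trial. All of this stands. It limits the point to what the collected data can support, and it means that no erroneous analysis is planned.

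A reader might go further and infer that tolerability, or safety, has no comparator at all. The documents do not support that: serious events, rash, gout flares and quality of life are collected in both arms. Nor do they support saying that the trial will report a false excess.

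It is also fair that the illustration rests on assumed rates. The article calls adverse reactions rare in treated patients, with the commonest at around 1%, so the upper rows of the table may well be too high.

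Finally, a self-reported item in an open-label trial is itself open to expectation and recall. That is true, and it limits what the fix can achieve. A count from both arms with a known bias is still more informative than a count from one arm. The objection does not remove the filter, and the tolerability objective still has no control information on these symptoms.

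**Conclusion.** The point holds, within limits. For non-serious symptomatic reactions other than rash and gout flares, chiefly nausea or vomiting, the rule and the no-drug control together leave the control count close to empty. Any difference between arms could not be distinguished from an artefact of the rule. That conclusion rests on the wording of the rule and on relatedness being judged with the arm known, not on any assumed rate.

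The size is not known. The range of about 1 to 10 percentage points is an illustration under equal true rates of 5% to 20%, with 20% to 50% of events attributed on allopurinol and 0% to 5% in control.

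Severity is minor to moderate: one part of a secondary objective is affected, and the primary analysis is not.

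**What to change.** - From the next annual questionnaire, which already asks about adverse events, record in both arms whether the named symptomatic reactions occurred (at least nausea or vomiting), regardless of presumed cause. This is the treatment already given to rash and gout flares.
- Compare arms on occurrence from that questionnaire, and use relatedness only for regulatory reporting. Keep reports from the six-week visit out of the comparison, since only one arm attends it.
- Present relatedness-filtered non-serious reactions as a description of the allopurinol arm, and state that they support no between-arm conclusion.
- Add a sentence reconciling the collection rule with the questionnaire section, so that it is clear which non-serious reports are kept.

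**Cost:** a few questionnaire items and two or three sentences of text. **Limits:** the data remain open-label self-report, recalled over up to a year, and asymptomatic liver-test rises are not covered. Earlier periods will be missing for patients who have already passed one or more questionnaires. The footnote to the eligibility box reports 52% of the target randomised by 4 April 2016, about 0.52 × 5215 = 2,712 patients, so this incompleteness should be reported with the results. If the items are not added, the third and fourth changes alone would still prevent misreading.
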